# Determining the feasibility of randomising infants, children and
young people to invasive and non-invasive urine sampling techniques (FROG):
Protocol for a multicentre randomised controlled feasibility trial and mixed
methods perspectives’ study of RCT feasibility.

**DOI:** 10.3310/nihropenres.14114.1

**Published:** 2025-11-21

**Keywords:** Paediatric, urinary tract infection, suprapubic aspirate, catheter, clean- catch, feasibility, RCT

## Abstract

**Background:**

Urinary tract infections (UTI) are the second most common serious bacterial
infection in children. When healthcare practitioners are unsure if an
infant, child, or young person has a UTI they perform a urine test. A
midstream sample is recommended by the National Institute for Health and
Care Excellence (NICE) for obtaining urine for testing. However, collecting
urine from children who are unable to provide a midstream urine sample is
challenging. Samples can be collected either by non-invasive (clean catch)
or invasive methods (trans-urethral bladder catheter or suprapubic
aspirate). Non-invasive methods are slow and prone to contamination but are
painless. Invasive methods are less prone to contamination and are quick but
can cause pain and distress.

**Methods:**

This is a mixed methods feasibility study comprising of three parts. Part 1
is a pragmatic multicentre randomised controlled feasibility trial. The
trial aims to evaluate the feasibility of conducting an RCT comparing
invasive and non-invasive sampling methods for infants, children and young
people (N = 100). Resource use will be assessed by parent reported
questionnaire and mixed methods descriptors reported by healthcare
professionals (n = 24). A cost analysis will assess the urine collection
methods, informing a future cost-effectiveness analysis. Part 2 is an
embedded mixed methods perspectives’ study including interviews with
parents (n = 15-20) and children (n = 10-15), five focus groups (n = 6-8 per
group) and interviews (n = 10) with healthcare professionals aiming to
assess feasibility and acceptability of the trial. Part 3 is a stakeholder
(n = 40) consensus meeting determining a final definitive study design.

**Discussion:**

The results of the study will inform a recommendation and decision on
progression and design of a definitive RCT for infants, children and young
people who have a suspected urine infection but cannot provide a midstream
urine sample.

**Trial registration:**

International Standard Randomised Controlled Trial Number (ISRCTN) 84676764:
Feasibility of conducting a randomised controlled trial (RCT) comparing
invasive and non-invasive urine sampling techniques in children under 16
years old with a suspected urinary tract infection ^
1
^.

## Background

Urinary tract infections (UTIs) are the second most common serious bacterial
infection in children, accounting for a substantial number of presentations to both
primary and secondary care ^
2
^. By age 16, approximately 1 in 10 girls and 1 in 30 boys will have
experienced a UTI ^
3, 4
^. Across childhood, the prevalence of UTI is estimated to be around 5% ^
5– 7
^, with symptoms often non-specific, including fever, vomiting, abdominal pain,
and lethargy ^
8, 9
^.

Urine testing is routinely performed when a UTI is suspected, guiding antibiotic
treatment and follow-up. Prompt diagnosis and management are essential to prevent
complications such as severe infection and renal scarring ^
10
^. NICE guidance (NG224, 2022) recommends clean catch urine (CCU) collection
where feasible, discouraging invasive methods such as transurethral bladder
catheterisation (TUBC) or suprapubic aspiration (SPA) unless non-invasive methods
are impractical ^
8
^.

Non-invasive methods are often preferred due to their painless nature and suitability
for primary care. However, CCU is associated with high contamination rates and is
time-consuming. Three UK studies involving 1,093 children reported contamination
rates of 26–36% for CCU samples ^
9– 12
^, compared to 12% for TUBC and 1% for SPA ^
9
^. Contaminated samples contribute to poor antimicrobial stewardship and
increased antimicrobial resistance (AMR), which has been identified by the World
Health Organisation as a major global threat ^
13
^.

E. coli is the predominant pathogen in paediatric UTIs. Resistance has increased,
with 30% of E. coli UTIs in England resistant to Trimethoprim and 10% to Cefalexin ^
8, 13
^. Reducing unnecessary antibiotic use is key to combating AMR. However,
reliance on contaminated non-invasive samples increases false positives, leading to
overtreatment, unnecessary investigations, hospital admissions, and distress for
families.

Internationally, approaches to urine collection vary. In Europe and North America,
national guidelines typically favour invasive methods ^
9– 12
^ due to their significantly lower rates of bacterial contamination ^
14– 18
^. Transurethral bladder catheterisation (TUBC) and ultrasonography-guided
suprapubic aspiration (SPA) are generally regarded as low-risk procedures in the US,
Europe, the Middle East, and Africa when performed by trained professionals ^
19, 20
^. Despite this, there is limited research exploring the views of
parents/guardians and healthcare professionals (HCPs) on invasive sampling, even
though such techniques have historically been described as emotionally and
physically traumatic for infants and families ^
19, 21, 22
^.

Recent UK data suggest that both HCPs and parents consider invasive methods
acceptable in febrile or seriously unwell children when a urine sample is urgently
required ^
23
^. Clean catch urine sampling, considered the gold standard non-invasive method
by UK HCPs, avoids painful procedures but can be distressing for infants and
stressful for parents managing the process ^
21, 23
^. These challenges may be heightened in time-critical emergency care
settings.

Despite the clinical importance of urine sampling, there is limited evidence
regarding the acceptability and feasibility of comparing invasive and non-invasive
methods in a UK context. A feasibility study is therefore required to determine
whether a definitive randomised controlled trial (RCT) comparing these approaches
can be conducted, and to inform its design.

## Design

This is a mixed methods feasibility study including three parts outlined in Figure 1 and Figure 2.

**Figure 1. f1:**
[figure not shown]
Study design phases; Parts 1, 2 and 3.

**Figure 2. f2:**
[figure not shown]
Flow diagram of the FROG mixed methods feasibility study involving three
linked parts. Work Package 1 (Part 1) is a randomised controlled feasibility trial, Work
Package 2 (Part 2) is a perspectives study, followed consecutively by Work
Package 3 (Part 3) stakeholder consensus meeting.

### Aim

To conduct a study of feasibility to assess which participants and interventions
should be included in a subsequent RCT, explore potential barriers to
recruitment and determine the feasibility of randomisation to invasive versus
non-invasive urine testing.

### Objectives

1. To determine the number of potential participants with suspected UTI
presenting to a range of clinical settings, including emergency care,
inpatients, and outpatients.2. To conduct a quantitative assessment of the ability to screen, recruit
and randomise children and young people to one of three interventions
(CCU, SPA and TUBC).3. To explore the views of parents, children, young people, and clinicians
on the acceptability of different collection methods, and the
appropriate population for inclusion in a future study.4. To identify potential barriers to recruitment and consent.5. To establish the most appropriate design, including important patient
centred outcomes, for use in a future study.6. To perform a cost analysis of the three urine collection methods to
inform the resource planning and design of a future cost-effectiveness
analysis.

## Methods

### Patient and Public Involvement

Patient and Public Involvement (PPI) groups in Northern Ireland, Liverpool
(Generation R) and via the GAPRUKI network contributed to the preparation of the
study design and outcomes. A total of eighty individuals including children,
young people, and adults were involved through a mixture of virtual meetings
(n=3) and surveys (n=2) prior to the study grant application.

PPI activity for the FROG study will include liaison with PPI groups from
charitable organisations and primary schools. A PPI competition will be held for
children to design a study logo and develop the trial identity which will then
be created by professional graphic designers. The PPI group will contribute to
the development of all participant information resources, the interpretation of
results, report writing and dissemination of study results and findings. A PPI
representative will be invited to participate in Trial Management Group meetings
and there will be a PPI representative on the Trial Steering Committee. PPI
representatives will be invited to participate in other relevant meetings and
the consensus meeting to ensure that the research is relevant to patients. PPI
members will be trained and supported for this role.

All members of the PPI group and PPI representatives will receive reimbursement
of expenses, in line with NIHR Centre for Engagement and Dissemination
recommendations. PPI representatives involved in the study management groups
will be acknowledged for their contributions. The Guidance for Reporting
Involvement of Patients and the Public, Version 2 (GRIPP2 checklists) ^
24
^ will be used for reporting on patient and public involvement (PPI) in the
publication reporting study results.

## Part 1

A pragmatic multicentre randomised controlled feasibility trial (n = 100) will assess
the feasibility of randomising children to invasive and non-invasive urine sampling.
The CONSORT ^
25
^ diagram depicting participant flow through the randomisation element of the
feasibility trial is presented in Figure 3 and
pictorial representation in Figure 4.

**Figure 3. f3:**
[figure not shown]
CONSORT diagram depicting participant flow through Part 1 (randomised
feasibility trial).

**Figure 4. f4:**
[figure not shown]
Pictorial representation of participant journey though the randomised
feasibility trial (Part 1).

### Primary outcome

The primary outcome is the proportion of participants who are offered the study
for whom consent to randomisation is obtained.

### Secondary outcomes

1. Age, gender, ethnicity and basic demographic data of participants who
consent

2. Proportion of presenting patients who are judged unsuitable for the study

3. Proportion of participants with consent for randomisation to CCU, TUBC or
SPA

4. Proportion of participants with consent for randomisation to CCU or TUBC
only

5. Proportion of participants with consent for randomisation to CCU or SPA
only

6. Proportion of participants in each randomised group who received the allocated
intervention

7. Rates of contamination by urine collection method

8. Safety as defined as the incidence of adverse events

9. Time to collect urine sample

10. Pain score associated with urine sampling

11. Final diagnosis of UTI

12. Resource use and costs

### Trial setting

The randomised controlled feasibility trial will be conducted at six hospital
sites in the UK.

### Trial population

Participants will be screened from attendances to paediatric EDs, assessment
units, inpatient wards, and outpatient clinics at recruiting sites. Neonatal
units will be excluded from recruitment. Patients assessed for eligibility and
reasons for exclusion will be recorded.

### Inclusion criteria

1. Child under 16 years of age at presentation.

2. Requiring urine testing for suspected UTI.

3. Cannot provide a mid-stream urine sample (are not toilet trained).

### Exclusion criteria

1. A clinical need to collect an immediate invasive urine sample without
delay

2. Participants where both methods of invasive urine sampling are deemed
inappropriate by the treating clinician or are unavailable.

3. Children sedated or admitted to intensive care units at the time of
screening

4. Language issues (not overcome with use of translators and available translated
information sheets).

5. Parent or legal representative unavailable to provide informed consent.

6. Consent declined.

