### Trial interventions

Eligible participants who consent to be randomised will be assigned to one of the
interventions; Invasive Trans-Urethral Bladder Catheterisation (TUBC) or
Invasive Suprapubic Aspiration (SPA) or Non-invasive Clean Catch Urine (CCU) (
Figure 3).

TUBC involves passing a flexible catheter into the bladder via the urethra. SPA
involves placing a needle through the skin of the abdomen directly into the
bladder. Non-invasive urine collection involves catching a urine sample in a
small dish. Sites will follow local policies and procedures for urine sampling
collection. In the event that a sampling method has been discontinued, an
alternative and clinically appropriate sampling method will be administered to
the child. Adherence to intervention and comparator will be recorded by
discontinuation of sampling method. These procedures are not protocolised and
will be performed, discontinued or modified in accordance with standard local
practice. Sampling method will be discontinued at the patient’s request
and guided by clinical judgement. Post-trial care will be provided as per
standard local clinical practice. A full summary of all trial interventions is
shown in Figure 5.

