## Discussion

Timely identification and management of urinary tract infections (UTIs) in infants,
children, and young people is essential to prevent adverse outcomes, including renal
scarring and long-term kidney damage ^
10
^. While midstream urine samples are preferred, many children are unable to
provide them necessitating alternative sampling methods. Non-invasive techniques
such as clean catch urine (CCU) are widely used in the UK but are associated with
high contamination rates and practical challenges ^
9– 12
^. In contrast, invasive methods such as transurethral bladder catheterisation
(TUBC) and suprapubic aspiration (SPA) yield cleaner samples ^
9
^, yet their acceptability and feasibility in routine UK practice remain
underexplored.

International guidelines often favour invasive sampling due to lower contamination
rates ^
14– 18
^, and these procedures are considered low-risk when performed by trained
professionals ^
9– 12, 23, 33
^. However, historical concerns about emotional and physical trauma ^
19, 21, 22
^ and limited UK-based evidence on parent and healthcare professional (HCP)
perspectives ^
23
^ highlight the need for a child-centred, context-specific approach. The FROG
feasibility study will address these gaps by evaluating the acceptability and
practicality of both invasive and non-invasive urine sampling methods in outpatient,
emergency, and clinic settings across the UK.

Using mixed methods and stakeholder involvement, the FROG study will assess
recruitment processes, sampling acceptability, and trial design feasibility. Upon
completion, progression to a definitive randomised controlled trial (RCT) conducted
in the UK will be guided by the following criteria:

(a) Willingness and ability of HCPs to screen and recruit eligible children during
Part 1 of the study. This will be demonstrated by recruitment of at least 33% of
eligible children.

(b) Mixed methods data on willingness to screen and recruit patients, from Part
2.

(c) Acceptability, or not, of the definitive study, including the invasive urine
sampling intervention to parents/guardians, to health care professionals as
evidenced by Part 2 data (mapped to the Theoretical Framework of Acceptability) and
Part 3 consensus data, as well as expressions of interest for the definitive
study.

(d) Development of recruitment and consenting procedures, with associated information
materials, that are acceptable to children/parents/guardians based on qualitative

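### Refusal and absence of a consenter are listed as exclusions, so the 33%-of-eligible progression threshold, read literally, does not respond to refusal

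*Protocol article*

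**What the plan says.** All references are to the protocol article.

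- **Exclusion criteria (Part 1).** The list ends with "5. Parent or legal representative unavailable to provide informed consent" and "6. Consent declined". Exclusion 2 also removes children for whom both invasive methods are inappropriate or unavailable.
- **Discussion, criterion (a).** The criterion is "a) Willingness and ability of HCPs to screen and recruit eligible children during" Part 1. The test is: "This will be demonstrated by recruitment of at least 33% of" eligible children. None of criteria (b) to (f) carries a number.
- **Primary outcome.** "The primary outcome is the proportion of participants who are offered the study" and "for whom consent to randomisation is obtained". Decliners are in this denominator. No progression threshold is attached to it.
- **Trial interventions.** "Eligible participants who consent to be randomised will be assigned to one of the" sampling methods. Here eligibility comes first and consent second.
- **Trial population and Informed consent procedure.** Patients assessed are logged and "reasons for exclusion will be recorded". Families who refuse randomisation are registered in the study system.

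**The concern.** An excluded child is not an eligible child. If exclusions 5 and 6 are applied as listed, a refusal turns a child who could have been recruited into one who was never eligible, and the same happens when nobody is present who can consent. Both are reasons for non-recruitment that a feasibility study sets out to measure; barriers to recruitment and consent are one of its stated objectives.

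At stake is the meaning of the one numerical progression rule. The same screening log could give a rate well above or well below 33%, depending on whether eligibility is judged before or after the consent discussion. The article supports both readings. If the choice is left until the data are in, the threshold loses its value as a rule set in advance.

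**Working it through.** **The plan's own figure.** There is nothing to reproduce. The 33% threshold has no stated derivation, and the sample size section says that no formal calculation was needed.

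**Inputs.** From the article: the 33% threshold, and a Part 1 target of 100. I take R = 100 children randomised; the conclusions depend only on ratios. Assumed, because the article gives no values:

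- consent rate among those offered, 5% to 50%, which fixes the number declining, D
- children with no consenter, U = 0 to 50
- children who meet the criteria but are never approached, M = 0 to 400

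**Formulas.**

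- Literal reading (exclusions 5 and 6 applied): R / (R + M)
- Eligibility judged before consent (5 and 6 not applied): R / (R + D + U + M)
- Primary outcome: R / (R + D)

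A child who is never approached has not declined, so M stays in the denominator on either reading.

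**Results with R = 100.**

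| Consent among offered | D | U | M | Literal | Before consent | Primary outcome |
|---|---|---|---|---|---|---|
| 5% | 1,900 | 0 | 0 | 100% | 5% | 5% |
| 10% | 900 | 0 | 0 | 100% | 10% | 10% |
| 20% | 400 | 0 | 0 | 100% | 20% | 20% |
| 50% | 100 | 0 | 0 | 100% | 50% | 50% |
| 50% | 100 | 0 | 100 | 50% | 33.3% | 50% |
| 50% | 100 | 50 | 100 | 50% | 28.6% | 50% |

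D and U do not appear in the literal formula, so neither can move that rate.

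**When the literal rule still fails.** It needs R / (R + M) < 0.33, that is M > R × (1/0.33 − 1) = 2.03 R. With R = 100, M = 203 gives 100/303 = 33.0% (pass), M = 204 gives 100/304 = 32.9% (fail), and M = 400 gives 100/500 = 20% (fail).

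**After correction.** With eligibility judged before consent, R = 100 passes only if D + U + M is at most 203, so at most 303 eligible children in all.

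**Why one denominator must govern.** Suppose 300 children meet the inclusion criteria and have no exclusion on clinical or language grounds. Of these, 60 have no invasive method available, 40 have no consenter, 120 decline and 80 are randomised (all assumed).

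- Literal: 80/80 = 100%
- Decliners restored: 80/(80 + 120) = 40%
- Children without a consenter also restored: 80/(80 + 120 + 40) = 33.3%
- Children without an available method also restored: 80/300 = 26.7%

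The same data fall on both sides of 33%.

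**The case against.** The strongest reply is that the literal reading is not the intended one. The Trial interventions section would be redundant if eligibility already included consent. Declined consent also recurs as an exclusion in Parts 2 and 3, which suggests a stock condition of entry rather than a definition of a denominator. This is plausible, but it does not remove the conflict: the Part 1 list still makes refusal an exclusion, and criterion (a) relies on eligibility without saying which sense applies. A fuller protocol might settle it. The point here, however, is that the stated passages disagree, not that detail is absent.

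Four stronger inferences are tempting, and the article does not support them.

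- *The threshold cannot fail.* It can, through children who are never approached. That is close to what criterion (a) says it measures, namely the willingness and ability of staff to screen and recruit.
- *Refusal is hidden from the study.* It is not. The primary outcome divides by those offered the study, decliners are registered, and criteria (b) to (f) and the consensus meeting also inform progression.
- *Decliners inflate secondary outcome 2.* That outcome concerns patients judged unsuitable. Nothing in the article says that refusals are coded there.
- *Exclusion for lack of an available invasive method is also an error.* This is a defensible choice. Under Assignment of intervention, a child needs at least one appropriate and available invasive method to be randomised at all.

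**Conclusion.** The concern holds in a limited form. Read literally, the exclusion list makes the 33% threshold insensitive to refusal and to the absence of a consenter. With every eligible child approached, it returns 100% whether 5% or 50% of families agree. It remains sensitive to children who are not approached, failing beyond about 2.03 such children per recruit. The primary outcome is unaffected, but it cannot stand in for criterion (a) because no threshold is attached to it.

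The insensitivity follows from the text alone. The sizes rest on the assumed consent rates and counts above, none of which the article supplies. The wording should be corrected before the progression decision is taken.

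**What to change.** 1. Remove exclusions 5 and 6 from the eligibility list. Record these children as eligible but not recruited, with the reason.
2. Before the progression decision, define the governing denominator of criterion (a) as all screened children who meet inclusion criteria 1 to 3 and are not excluded by criteria 1 to 4, whether or not they were approached.
3. Show children excluded only because no invasive method was available as a separate line in the screening flow, and give a supplementary rate that includes them. State that this rate is supplementary and does not govern.

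The cost is protocol wording and screening-log codes. No extra patients or visits are needed, because refusals and reasons for exclusion are already to be recorded. The drawback is that the recruitment rate will look lower than on the literal reading.

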### Sample size

As a feasibility study, a formal sample size calculation is not required. A
target of 100 participants in Part 1 of the study is based on the need to
recruit enough participants to Part 2 who both consent and decline to
randomisation.

